141 score is 5. A higher score represents higher perceived safety.

142 *Drug Effectiveness*

- 143 ○ Single question with a 5-point Likert scale response for "In  
144 your opinion, how *effective* is Mifeprex, when taken correctly,  
145 for ending an early pregnancy?" Minimum score is 1.  
146 Maximum score is 5. A higher score represents higher  
147 perceived effectiveness.

148 The full survey questionnaire can be found in Appendix 3.

149 **Survey pretest.** The PMI designs and survey questions were pretested  
150 with a convenience sample of the research team's social network  
151 (colleagues, family, friends). After revision, in response to this feedback, a  
152 pilot study of 30 participants was recruited on the Prolific platform to test  
153 the revised survey and inform power calculations for the study, which will  
154 use the same platform. No one who participated in the pilot will be eligible  
155 for inclusion in the main study.

156 **Analyses.** We will compare outcomes across the different PMI formats,  
157 first with a Kruskal-Wallis test for mean differences, followed by a Mann-  
158 Whitney test for pairwise comparisons. We will use a Bonferroni-  
159 correction to account for multiple comparisons,  $\alpha = .01$  for ordinal  
160 variables. Additionally, we will conduct sensitivity analyses to assess  
161 changes in the primary outcomes (usefulness and comprehension): (1)  
162 including individuals who are excluded due to completing the survey too  
163 quickly ( $< 6.97$  minutes, which represents the 10th percentile of  
164 completion time from the pilot data collection) and (2) excluding  
165 individuals who report not believing in using abortion medication under  
166 any circumstance (Appendix 3 #14), as they are unlikely to belong to the  
167 potential user population. To assess the distribution of the individuals  
168 participating in this study, optional questions regarding demographic  
169 information and the study participant's previous exposure Mifeprex (i.e.,  
170 *Have you or someone you care about ever used the drug described in the*  
171 *medication guide?*) will be asked at the end of the survey. We will assess  
172 whether the Qualtrics randomization function was successful by checking  
173 the distribution of participants among the PMI groups. We should expect  
174 to see even distribution in group allocation, and approximately 30% of

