175 each group to have at most a high school education. Other characteristics  
176 should be similarly distributed across study groups.

177 Based on response variance in our pilot study, a sample size of 100  
178 participants per condition will yield statistical power with at least 85%  
179 chance of detecting a 0.5-point difference in comprehension (with a  
180 minimum score of 0 and maximum score of 7) between the *FDA PMI* and  
181 *Vendor PMI* group, assuming a two-sided  $\alpha = .05$ .

182 We hypothesize that the *FDA PMI* and *Decision Critical PMI* will be  
183 perceived as more readable and demonstrate greater comprehension than  
184 the *Vendor PMI*, as these formats are designed with readability and  
185 comprehension in mind. Additionally, we anticipate the *Decision Critical*  
186 *PMI* will be rated as more useful in supporting decision-making than the  
187 other two PMI formats. We do not anticipate differences in supporting  
188 proper drug use since supporting use is the primary goal of the *Vendor* and  
189 *FDA PMI* formats.

190 All analyses will be conducted using R Statistical Software (v4.3.2).

191 **Ethical considerations.** This study received expedited review and  
192 approval by Carnegie Mellon University's Institutional Review Board  
193 (STUDY2023\_00000449). The study protocol was registered on  
194 ClinicalTrials.gov (NCT06320808) and followed the Consolidated  
195 Standards of Reporting Trials (CONSORT) guidelines.

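### Power for the comprehension comparison is stated at alpha .05, but the only test level in the analysis plan is .01; if .01 governs, the stated inputs guarantee about 66% power, not 85%

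*Protocol*

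**What the plan says.** Section 6.0 of the protocol (Analyses and Data Management) fixes a significance level in two neighbouring places.

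- **Analyses paragraph.** All outcomes are compared "first with a Kruskal-Wallis test for mean differences", then by pairwise Mann-Whitney tests, with a Bonferroni "correction to account for multiple comparisons, $\alpha = .01$ for ordinal" variables. No other test level appears there.
- **Sample-size paragraph.** 100 "participants per condition will yield statistical power with at least 85"% "chance of detecting a 0.5-point difference in comprehension" between FDA PMI and Vendor PMI, on a score from 0 to 7, at two-sided alpha .05. The variance is said to come from the pilot study, but no SD is printed.

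The 0-7 range matches the seven-item score for knowledge common to all PMIs (questions 1, 2 and 6-10). Section 1.0 gives a total sample of 330 and Section 4.0 a 1:1:1 allocation, so 110 per arm.

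**The concern.** This is the protocol's only power statement, and it supports the first primary research question in Section 3.0 (FDA PMI against Vendor PMI). If that comparison is tested at .01, the quoted power belongs to a more lenient test than the one planned. A null result would then be read as coming from a comparison with at most a 15% chance of missing a true 0.5-point difference. At the boundary of the stated inputs, the chance of missing it would be about one in three.

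**Working it through.** **Inputs from the protocol:** difference 0.5; n = 100 per arm (110 if all 330 are analysed); power at least 85% at two-sided .05; planned level .01. **Assumptions:** normal approximation with a common SD. The SD is back-solved and is not a figure in the protocol.

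**1. Reproduce the stated figure.** The 85% cannot be checked independently without the SD. Solving for it:

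SD = 0.5 / ((1.9600 + 1.0364) × √(2/100)) = 0.5 / (2.9964 × 0.1414) = 1.18.

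Since the protocol says at least 85%, its inputs imply SD ≤ 1.18.

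**2. Same inputs at two-sided .01.**

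- n = 100: Φ(2.9964 − 2.5758) = Φ(0.4206) = 66.3%.
- n = 110: Φ(2.9964 × √1.1 − 2.5758) = Φ(0.5668) = 71.5%.

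The noncentral t calculation gives 65.9% and 71.2%.

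**3. If the 85% was computed for a t-test.** Assume a Mann-Whitney efficiency of 0.955, the value for normal data:

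- n = 100: Φ(2.9964 × √0.955 − 2.5758) = Φ(0.3524) = 63.8%.
- n = 110: 69.0%.

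**4. If the pilot SD is below the boundary** (normal approximation):

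| Power at .05, n = 100 | Implied SD | Power at .01, n = 100 | Power at .01, n = 110 |
|---|---|---|---|
| 85% | 1.18 | 66.3% | 71.5% |
| 90% | 1.09 | 74.7% | 79.5% |
| 95% | 0.98 | 84.8% | 88.6% |

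So 85% power at .01 with 100 per arm would need about 95% power at .05, which the protocol does not claim.

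**5. Detectable difference** with 85% power at .01, n = 100, at the boundary SD: (2.5758 + 1.0364) × 1.18 × √(2/100) = 0.60 points.

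**6. Which n applies.** The Analyses paragraph excludes people who finish in under 6.97 minutes, the pilot's 10th percentile. If the main study loses a similar tenth, 330 × 0.9 = 297, or 99 per arm. The protocol does not say that the extra 30 are an allowance for this, so both columns are shown.

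**The case against.** **The 85% is a floor.** A reader might infer that power at .01 is 66% or lower. The protocol does not support that. Because the claim is at least 85%, about 66% is the lowest normal-theory value its inputs allow at n = 100. Power falls below it only with a rank-test loss, or if the true SD exceeds 1.18.

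**The .01 is tied to ordinal variables.** Six outcomes are single 5-point items, whereas comprehension is a count of correct answers, and the protocol never classifies the count. This stands, and it makes the finding conditional. Still, comprehension gets the same rank tests and no other alpha is given for it, so .01 is the best-supported reading. A reader might go further and infer that, if .05 was meant, comprehension has no multiplicity control. That does not follow: the Bonferroni correction is announced in general terms, and a statistical analysis plan that is not at hand may give the level for other variables.

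**The Kruskal-Wallis step.** A reader might infer a further loss because that test must first be passed at .01. The text gives only an order of tests. It sets no threshold and does not make the pairwise tests conditional, so no such loss is counted here.

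**The method behind the 85% is not stated.** If it was already rank-based, the reduction in step 3 would count the same loss twice. That step is therefore only a conditional figure.

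**Nothing is miscalculated.** The .05 is openly labelled, and an optimistic power statement neither biases estimates nor inflates the type I error. That is true and limits the harm, but the stated power still does not match the only test level in the plan.

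**Conclusion.** Wrong as written: the only power statement uses .05, while the only test level in the analysis plan is .01, and the protocol does not reconcile them. If .01 governs the FDA PMI against Vendor PMI comprehension test, the stated inputs guarantee about 66% power at 100 per arm and about 71% at 110, or about 64% and 69% if the 85% came from a t-test. These are boundary values. They rest on a back-solved SD of 1.18 and on .01 applying to the 0-7 score, which is likely but not stated. Actual power is higher if the pilot SD is smaller.

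A minor accompanying point: Kruskal-Wallis compares rank distributions and is not a test of means.

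**What to change.** - In the Analyses paragraph, state that the FDA PMI against Vendor PMI comprehension test uses the Bonferroni alpha. If another alpha governs it, name that alpha and the multiplicity control that then applies.
- In the sample-size paragraph, print the pilot SD. Restate the power for 0.5 points, or the difference detectable with 85% power, at that alpha for the Mann-Whitney test and the number expected to be analysed. The figure must come from the actual pilot SD; the 66% and 0.60 points above only show the boundary.
- Describe Kruskal-Wallis as a test of differences in distribution.

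The cost is wording only. If .01 governs, the stated power becomes less favourable unless the pilot SD was about 0.98 or less. No increase in enrolment is needed.

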## 196 7.0 Consent Process

197 Participants will be provided with a consent page describing the purpose of the  
198 study and the procedure of the research. The informed consent page can be found  
199 in Appendix 4. Survey participation is entirely voluntary.  
200  
201  
202  
203  
204

205 8.0 Appendices

206 **Appendix 1.** Recruitment language within the Prolific Platform.

207

208 This survey is being conducted by [name] at Carnegie Mellon University,  
209 and [name] at the University of Pittsburgh. The purpose of the research  
210 is to better understand information provided with different medications. In this survey,  
211 you will be asked to read a consent form, view a document containing information about  
212 a medication, and answer a series of questions about the information you see on the  
213 document, and then answer demographic questions. This survey will take half an hour to  
214 complete, and you will be compensated \$10.

215

216

**Appendix 2.** Study attention check.

**Attention Check**

We want to make sure that a human, and not a bot, is responding. **Please select the very last response (option 4) to the question below.** If you do not pass this attention check, you will not be eligible to continue and will be routed out of the survey. Following, your participation in the study, you will receive compensation within 1 week.

After reading the above paragraph, which is the correct option?

- ☐ Option 1
- ☐ Option 2
- ☐ Option 3
- ☐ Option 4

**Appendix 3.** Study survey questions and response options.

**About this study**

The U.S. Food & Drug Administration (FDA) will soon start providing people with new medication guides when they pick up prescription medication from the pharmacy. We are interested in your feedback on how well the guides work. The results from this survey will help us to make suggestions on how to improve the design of these guides. The next page shows an example of a prescription medication guide for a drug called Mifeprex.

Please read the guide and answer the questions that follow as best you can. You'll be able to look at the guide when you answer the questions.

Take a moment to read through the medical guide shown below. You can download the medical guide from the link below and open it in a separate window if you would like to refer to it while you complete the survey questions. The guide will also be shown again on the following pages, beneath each survey question.

[Randomized PMI for Mifeprex is shown]

Now we will ask you some questions about Mifeprex. It is possible that some of these answers are not available on the guide you just saw. Please answer as best you can and, if you are not sure of an answer, it is ok to select or type "Unable to locate information." If you need it, the guide will be available to look at below each question.

**1. What is Mifeprex used for?**

- ☐ To end an early pregnancy, up to 6 weeks
- ☐ To end an early pregnancy, up to 10 weeks
- ☐ To end a pregnancy in the first or second trimester
- ☐ To end a pregnancy at any time before delivery
- ☐ Unable to locate information

**2. How should Mifeprex be taken?**

- ☐ Take one tablet of MIFEPREX and then take 2 more tablets of MIFEPREX 24-48 hours later
- ☐ Take one tablet of MIFEPREX and then take 4 tablets of another drug called misoprostol 24-48 hours later
- ☐ Take 3 tablets of MIFEPREX at once
- ☐ Take 3 tablets of MIFEPREX over a 48 hour period
- ☐ Unable to locate information

**3. What percentage of people taking Mifeprex experience a serious side effect?**

Please enter a number. *If you cannot find the information, please skip this question and move onto the next.*

**4. Which statement is correct about how well Mifeprex works?**

- ☐ MIFEPREX when combined with misoprostol ends all pregnancies.
- ☐ MIFEPREX, when combined with misoprostol, ends 97.4 % of pregnancies
- ☐ MIFEPREX ends 100% of pregnancies without any complications.
- ☐ MIFEPREX ends 90% of pregnancies, but the rate of birth defects is 10%
- ☐ Unable to locate information

**5. How many people participated in the clinical studies examining the effectiveness of Mifeprex? Please enter a number. If you cannot find the information, please skip this question and move onto the next.**

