| Study Title                                        | Evaluating FDA's Proposed Patient Medication Information Handout: A Randomized Trial Measuring Perceived Usefulness and Comprehension                                                                                                                                                                                                                                                                                                                                                                                                                                                                                                                                                                                                                                                                                                                                                                                                                                                                                                                                                            |
| Study Design                                       | 
Allocation: Randomized
 
Interventional Model: Parallel Assignment
 
Interventional Model Description: Participants will be randomized to receive either the one-page FDA-template PMI (FDA PMI), a modified template, which added quantitative information about drug risks and benefits (Decision Critical PMI), or the existing drug information insert (Vendor PMI – available at: https://www.fda.gov/media/164654/download).
 
Participants will complete the same survey questions measuring usefulness, comprehension of the information, and perceived strength of the regulatory evidence.
 
Masking: Single (Investigator)
                                                                                                                                                                                                                                                                                                                                             |

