## 2.0 Background

In Fall 2023, FDA proposed amending its current prescription drug labeling regulations to facilitate patient decision-making. It would require drug companies to provide patient medication information (PMI) in a new template. FDA proposed a one-page document that highlights the “essential information that patients need to know about the prescription drug product, including basic directions on how to use the product safely and effectively.” When evaluating drugs for approval, FDA uses a Benefit-Risk Framework (BRF). The BRF considers risks, benefits, and alternatives for a drug. FDA references the BRF as guiding development of the new PMI, which largely aligns with the BRF. However, the current proposal does not contain information regarding a drug’s *benefit*, thereby omitting critical information for patients’ decision-making. FDA’s proposal also does not include any quantitative estimates of the medication’s risks or benefits, which decision science research has demonstrated that people utilize in their decision-making process. Additionally, the proposal does not require user testing of PMIs.

We aim to address these issues by (a) extending the proposed PMI to include benefit information and quantitative information about safety and effectiveness and (b) demonstrating a simple procedure for user testing. Using Mifeprex (generic: Mifepristone) as a case study, we demonstrate the procedure with a medication that is FDA-approved, safe, and effective medication for abortion and miscarriage management up to 10 weeks’ gestation.

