**10. How long should a woman who has taken Mifeprex expect vaginal bleeding or spotting?**

- ☐ 24 to 48 hours
- ☐ 9 to 16 days
- ☐ 9 to 20 days
- ☐ 10 weeks
- ☐ Unable to locate information

The next set of questions ask your opinion about the drug, Mifeprex, that was described in the prescription medication guide you just saw.

**11. In your opinion, how strong is the *scientific evidence* that Mifeprex, when taken correctly, helps patients end an early pregnancy?**

- ☐ Very weak
- ☐ Weak
- ☐ Neither weak nor strong
- ☐ Strong
- ☐ Very strong

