**13. In your opinion, how *effective* is Mifeprex, when taken correctly, for ending an early pregnancy?**

- ☐ Extremely effective
- ☐ Somewhat effective
- ☐ Neutral/Not sure
- ☐ Somewhat ineffective
- ☐ Very ineffective

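### Item 4 shows every arm one quantified benefit figure, 97.4%, before perceived effectiveness is rated, and it can be answered by elimination; this may attenuate the FDA PMI versus Decision Critical PMI contrast

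*Protocol*

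**What the plan says.** The Protocol's Study Summary (section 1.0) gives all arms one instrument: "Participants will complete the same survey questions measuring usefulness, comprehension of the information, and perceived strength of the regulatory evidence". It describes the Decision Critical PMI as "a modified template, which added quantitative information about drug risks and benefits (Decision Critical PMI"). Section 2.0 says of FDA's template that "the current proposal does not contain information regarding a drug’s *benefit" and that it "does not include any quantitative estimates of the medication’s risks or benefits".

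Section 6.0 splits the ten comprehension items into two scores. Items 1, 2 and 6-10 form the knowledge common to all guides (0-7). Items 3-5 form the Quantified Risk/Benefit Knowledge score.

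In Appendix 3, item 4 asks how well the drug works. One option is "MIFEPREX, when combined with misoprostol, ends 97.4 % of pregnancies". The other three substantive options claim that all pregnancies are ended, that there is complete success with no complications, or a 90% success rate paired with 10% birth defects. A fifth option lets the participant say that the information could not be located. Items 3 (serious side-effect rate) and 5 (number of trial participants) are open numeric entries that may be skipped.

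The opinion items come after items 1-10. Item 11 begins "In your opinion, how strong is the *scientific evidence* that" and item 13 asks "In your opinion, how *effective* is Mifeprex, when taken correctly, for ending an early pregnancy". No arm-specific wording and no randomised item order are described.

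**The concern.** The second primary research question in section 3.0 compares the FDA PMI with a version that adds quantified risk and benefit information. For that comparison to be clean, participants in the FDA PMI arm should not meet such a figure elsewhere before they are assessed. Item 4 shows them one.

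Two outcomes are exposed. First, an FDA PMI participant who believes the printed figure may rate effectiveness on item 13 more as a Decision Critical PMI participant would. Second, item 4 can earn credit for a fact that the guide did not supply, because only one option is a precise percentage without an absolute or implausible claim attached.

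Both effects pull towards no difference. A null result on item 13 would then be ambiguous: either the added numbers do not change opinion, or the questionnaire supplied one of them to the comparator. The planned sensitivity analyses cannot separate these, because every participant sees item 4.

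**Working it through.** **The plan's own power figure.** Section 6.0 states at least 85% power with 100 per condition for a 0.5-point difference on the 0-7 score, at two-sided alpha .05. The pilot SD is not given, so the figure cannot be reproduced; only the SD that it implies can be found: 0.5 / (√(2/100) × (1.960 + 1.036)) = 0.5 / 0.424 = 1.18. This figure concerns FDA PMI versus Vendor PMI on items 1, 2 and 6-10. Item 4 is not among them, so the figure is untouched. The plan states no power for item 13 or for the quantified score.

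**What is and is not shown.** Of the three quantified items, only item 4 prints a figure. Items 3 and 5 are open entry, so the side-effect rate and the trial size are not disclosed. Scoring items 3-5 apart from the common knowledge implies that at least one guide lacks their content. Section 2.0 points to the FDA template as such a guide.

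**Item 13, illustration.** Assume that a share c of the FDA PMI arm takes up the figure and then answers as the Decision Critical PMI arm would. The difference D shrinks to D(1 − c). With n per arm, power ≈ Φ(D(1 − c)/(SD × √(2/n)) − 2.576) at two-sided alpha .01, the level that section 6.0 sets for ordinal variables. This is a normal approximation to the planned Mann-Whitney test. Assumed: D = 0.5 points. From the plan: n = 100.

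| SD (assumed) | c = 0 | c = 0.25 | c = 0.50 |
|---|---|---|---|
| 0.8 | 96.7% | 77.0% | 35.7% |
| 1.0 | 83.1% | 53.0% | 21.0% |
| 1.2 | 64.4% | 35.7% | 13.5% |

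For example, at SD 1.0 and c = 0.25: 0.375/0.1414 − 2.576 = 0.076, and Φ(0.076) = 0.530. With 110 per arm (330/3) and SD 1.0, the three values are 87.1%, 58.1% and 23.5%.

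**Quantified score, illustration.** Assume one point per item. In the Decision Critical PMI arm a share h finds each answer, and in the FDA PMI arm nobody does. Among participants in either arm who lack the answer to item 4, a share g marks the 97.4% option. On item 4 the Decision Critical PMI arm scores h + (1 − h)g and the FDA PMI arm scores g, a gap of h(1 − g). Items 3 and 5 each keep a gap of h. The total gap is h(3 − g) instead of 3h, so the proportion lost is g/3:

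- g = 0.25 (random choice among the four substantive options): 0.25/3 = 8%.
- g = 0.50: 17%.
- g = 1 (everyone eliminates correctly): 33%, the ceiling.

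The documents give none of c, g, h, D or the SD for these outcomes.

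**The case against.** The strongest reply is that seeing an answer option is not the same as receiving information. The figure is never confirmed as correct. The instructions before item 1 warn that some answers may not be in the guide and allow participants to say so. The guide stays in view under each question, and the opinion items are introduced as being about the drug that it described. An FDA PMI participant rating item 13 has at most the memory of an option nine items back. This stands. It makes uptake uncertain, and it makes the dilution model an upper bound for any given c, because the model treats a participant who took up one number as if the whole Decision Critical PMI had been read.

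A reader might infer that the questionnaire hands the FDA PMI arm everything that defines the Decision Critical PMI. The documents do not support that. The definition covers quantified risks and benefits, and item 4 shows one benefit figure. Item 11 is also only loosely exposed: trial size bears more directly on strength of evidence than an efficacy percentage does, and it is not disclosed.

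A reader might also treat items 11 and 13 as settled primary outcomes. Section 6.0 lists them under that heading, but its text on sensitivity analyses names only usefulness and comprehension, and no stated hypothesis concerns them. The item 4 score belongs to comprehension and is primary on either reading.

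Finally, the bias is conservative: a Decision Critical PMI advantage that was found would stand. This is correct, but it does not help with reading a null result.

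**Conclusion.** The point holds in a limited form. Item 4 exposes all arms to one quantified benefit figure before item 13 and, with a weaker link, item 11. It can also be answered without the guide. This may attenuate the FDA PMI versus Decision Critical PMI contrast on item 13 and on the quantified score.

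The size cannot be stated from the documents. The power losses in the table depend on an assumed difference, SD and uptake. The loss on the quantified score runs from nil to one third under the equal-difficulty assumption. The direction, towards no difference, assumes that the figure moves opinion in the FDA PMI arm the way it does in the Decision Critical PMI.

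That 97.4% is the keyed answer, stands in the Decision Critical PMI and is absent from the FDA PMI is a strong inference from section 2.0, the scoring split and the other options. It is not stated text, because the guides are not shown. The content of the Vendor PMI on this point is unknown. The finding does not invalidate the comparison and changes no stated figure; it is a cheap improvement worth making.

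**What to change.** Make item 4 an open numeric entry in the format of items 3 and 5, for example: *What percentage of pregnancies are ended by Mifeprex when combined with misoprostol?* Offer a skip or a way to say that the information could not be located. No arm is then shown a figure, and elimination is no longer possible.

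If multiple choice is kept, offer several equally plausible percentages and ask items 11-13 before items 3-5. The reordering protects the opinion ratings. The new options prevent elimination but still leave a chance of guessing correctly.

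The cost is one reworded item before launch and a numeric scoring key that says whether rounded entries count. Item 4 would no longer be comparable with the pilot version. The 0-7 score used for the power calculation is not affected.
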